**Population:**

Patients eligible for TORS and CPAP or MAD aged >18 years with moderate to severe OSA (Apnea Hypopnea Index >15) untreated before.

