### Eligibility criteria

2.2

All patients presented at the otorhinolaryngology department of the Frisius Medical Center with a diagnosis of moderate to severe OSA eligible for surgery based on physical examination, respiratory polygraphy (PG) and drug induced sleep endoscopy (DISE) will be screened for eligibility. Inclusion criteria include [1]: age of at least 18 years or older [2]; ability to understand and comply with the protocol requirements, and provide written informed consent [3]; AHI of equal to or more than 15 on PG [4]; physical examination showing lingual tonsils classified as Friedman grade 3 or 4; and [5] DISE demonstrating collapse at BOT level classified as grade 2. Exclusion criteria include [1]: body mass index higher than 32 [2]; concentric collapse during DISE [3]; symptoms of Central Sleep Apnea Syndrome [4]; high co-morbidity as determined by American Society of Anaesthesiologists (ASA) score of 4 (severe systemic disease that is a constant threat to life) [5]; history of psychiatric hospitalization [6]; excessive use of opiates or benzodiazepines; and [7] previous treatment of CPAP and/or MAD or inability to tolerate MAD.

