### Study outcomes

2.5

The primary endpoint of this study is the mean AHI measured 6 months post-intervention. This time point was selected because it reflects the earliest clinically relevant assessment at which treatment effects are expected to be stable in both arms: after postoperative recovery following TORS and after establishment of CPAP/MAD use and adherence. The PG will be performed at baseline, 6 months and 12 months. A lower AHI reflects improved airway patency and is thus clinically meaningful in assessing treatment effectiveness between groups. Twelve month follow up is included as an important secondary endpoint to evaluate durability of treatment effects in this chronic condition. Secondary outcomes include: (1) 50% reduction of AHI at 6 months compared to baseline and or AHI below 20/h (Sher's criteria) [2,21] reduction of AHI at 12 months to <5/h will be defined as surgical cure [3,22] differences in mean ODI 4% values at 6 months and 12 months, and reduction of ODI 4% to 25% relative to baseline will be defined as clinically relevant [4,22] differences between FOSQ-35 [15] scores at 3 months, 6 months and 12 months in which an increase of 10% of the score compared to baseline on the FOSQ-35 questionnaire will be defined as clinically relevant [5,22] differences between scores of ESS at 3 months, 6 months and 12 months and a reduction on the ESS to <10 will be defined as clinically relevant [6,23] differences between scores of quality of life questionnaires EQ-5D-5L [19] at 3 months, 6 months and 12 months [7]; differences in scores on the visual analogue scales (VAS) for snoring, tiredness and globus in all patients between baseline, 3, 6 and 12 months [8]; VAS scores swallowing and taste for patients in the TORS group at baseline compared to 3 months, 6 months and 12 months.

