### Sample size calculation

2.8

To answer our primary objective 25 patients per arm must be included in the study. This sample size calculation is based on results of an earlier RCT where OSA surgery was compared to conventional therapy (medical management) [26]. At 6 months MacKay et al. found the means of AHI to be in group 1, the conventional group 34.5 with a standard deviation of 23.0 and in group 2, the surgery group 20.8 with a standard deviation of 18.4. We have chosen to select a smaller standard deviation compared to the literature, as retrospective analysis of our database of OSA patients treated with TORS show a mean of AHI at 3 months (n = 31) of 16.4 with a standard deviation of 12.0 and a mean of AHI at 1 year (n = 14) of 10.8 with a standard deviation of 8.48. As our inclusion and exclusion criteria are strict and like our retrospective data and we expect a similar outcome. Given the sample size, analyses will primarily focus on estimating treatment effects with 95% confidence intervals. Secondary outcomes and subgroup analyses will be considered exploratory. Group sample sizes of 21 and 21 achieve 82% power to detect a difference of 10.0 between the null hypothesis that both group means are 34.0 and the alternative hypothesis that the mean of group 2 is 24.0 with estimated group standard deviations of 10.0 and 12.0 and with a significance level (alpha) of 0.05 using a two-sided two-sample *t*-test. The detectable differences are estimated to be of clinical relevance. To correct for possible missing data, we calculated a 20% bigger sample size which results in a sample size of 25 patients per arm.

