### Statistical analysis

2.10

All statistical analyses will be conducted using IBM SPSS Statistics. The full analysis set (FAS) follows the Intention-To-Treat (ITT) principle and includes all planned subjects, except those with major protocol violations, no post-baseline data, or no study intervention.

Baseline characteristics, including age, gender, BMI, PG, ENT exam, DISE results, smoking, and reflux history, will be summarized using descriptive statistics. Quantitative variables will be presented as mean and standard deviation or as median with interquartile range or minimum/maximum, and qualitative data as frequencies and percentages, with 95% confidence intervals where applicable. Data normality will be assessed graphically and numerically. No formal statistical tests will be performed for baseline comparisons. The primary outcome (AHI at 6 months) will be analysed using independent *t*-test or Mann-Whitney *U* test depending on data distribution. Given the RCT design, adjustments for baseline differences are not foreseen. In case of missing data this will be mentioned in the results. Missing data will not be replaced. For all hypothesis testing, a two-sided p-value of less than 0.05 indicates statistical significance. Secondary outcomes will follow the same approach. For continuous variables, appropriate group comparisons (*t*-test, Mann–Whitney U, ANOVA, or Kruskal–Wallis) will be used. For categorical outcomes, Fisher's exact or Chi-square tests will be applied as applicable. Because the control arm includes two standard non-surgical modalities (CPAP and MAD), additional prespecified analyses will be performed to assess robustness. These include [1] subgroup analyses comparing TORS vs CPAP and TORS vs MAD separately (exploratory due to sample size) and [2] sensitivity analyses adjusting for control modality (CPAP vs MAD) when evaluating the primary endpoint. Treatment adherence data will be reported descriptively and considered when interpreting outcomes. Other study parameters will be analysed descriptively as outlined above.

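### The 6-month AHI responder rule joins its two conditions with 'and or', which leaves two different endpoints; since entry starts at AHI 15, the 'or' reading can be met before any treatment

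*Protocol article*

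**What the plan says.** Section 2.5 (Study outcomes) makes mean AHI at 6 months the primary endpoint. The first item in its list of secondary outcomes is "50% reduction of AHI at 6 months compared to baseline and or AHI below 20/h", labelled "Sher's criteria". The article does not spell those criteria out. The other AHI threshold in the list, below 5/h, applies at 12 months, so this is the only AHI responder rule at 6 months.

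Section 2.2 (Eligibility criteria) requires "AHI of equal to or more than 15 on PG"; the abstract has "moderate to severe OSA (Apnea Hypopnea Index >15". On either version, patients with AHI between 15 and 20 can enter.

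Section 2.10 (Statistical analysis) states: "For categorical outcomes, Fisher's exact or Chi-square tests will be applied as applicable". The responder rule would therefore be compared between arms as a proportion, at the two-sided 0.05 level set for all testing. Section 2.8 (Sample size calculation) limits its weight: "Secondary outcomes and subgroup analyses will be considered exploratory".

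**The concern.** A responder rule has to give one answer for each patient. With *and or* between the conditions, the same pair of AHI values can be a response or a non-response depending on the reader.

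The *or* reading also fits this population badly. Its threshold of 20/h lies above the entry limit of 15/h, so part of the enrolled range meets the rule at baseline.

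What is at stake is the responder proportion in each arm, and the comparison between arms built on it. The trial is unblinded (section 2.9), so a connective left open could be settled after the results are known. This is a risk in choosing the definition and not in measurement, because both conditions are computed from the same polygraphy values.

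**Working it through.** **The plan's own figure.** The only power figure in the article belongs to the primary endpoint: "Group sample sizes of 21 and 21 achieve 82% power to detect a difference of 10.0", with SDs 10.0 and 12.0. The standard error is √(100/21 + 144/21) = √11.619 = 3.409. The noncentrality is 10/3.409 = 2.93 on 40 degrees of freedom, and power is 81.7%. The stated 82% reproduces. No figure is stated for the responder rule.

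**Logic of the rule.** Let b be baseline AHI and f the 6-month AHI. Condition A is f ≤ 0.5b; condition B is f < 20.

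| Baseline | Relation | *A and B* becomes | *A or B* becomes |
|---|---|---|---|
| b < 40 | A implies B, since 0.5b < 20 | 50% reduction | AHI < 20 |
| b ≥ 40 | B implies A, since 20 ≤ 0.5b | AHI < 20 | 50% reduction |

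The readings therefore differ across the baseline range, and not only near the entry limit.

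**Worked cases.**
- 16 to 19: A needs f ≤ 8 and fails; B holds. Response under *or*, none under *and*.
- 80 to 40: A holds (40 ≤ 40); B fails. Response under *or*, none under *and*.
- Any entry value from 15 to <20 with no change: B holds before treatment. Under *and* the same patient must fall to half of baseline, that is to between 7.5 and just under 10.

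These results need no distributional assumption.

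**Size, by simulation.** Follow-up values come from section 2.8. One set is the planning value of 24.0 with SD 12.0. The other is the centre's own TORS series at 3 months, 16.4 with SD 12.0 (n = 31). Section 2.8 supposes "both group means are 34.0 and the alternative hypothesis that the mean of group 2 is 24.0". I read 24.0 as the surgical mean, because the preceding sentences of 2.8 call surgery group 2; sections 2.1 and 2.9 number the arms the other way round.

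Assumed, and not in the article: lognormal baseline with (mean, SD) of (34, 15), (34, 10) or (28, 12) cut at 15, which gives means of about 30 to 35 after the cut; gamma follow-up; baseline–follow-up correlation 0.3 or 0.6 through a normal copula.

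| TORS follow-up | *and* | *or* | Of 25 patients |
|---|---|---|---|
| 24.0, SD 12.0 | 15–26% | 44–49% | about 4–7 v 11–12 |
| 16.4, SD 12.0 | 50–60% | 72–76% | about 13–15 v 18–19 |

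A second model used baseline 15 plus a gamma variable (mean 34, SD 10 to 15), lognormal follow-up and correlation 0 to 0.7. It gives 14–27% v 46–50% and 56–63% v 75–79%. With a lower baseline in that model (mean 28, SD 10), the gap widens to 7–18% v 45–46% and about 49% v 75%.

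**What makes up the gap.** In the lognormal model 4%, 11% or 19% of patients enter below 20/h, depending on the baseline chosen. That is the share who could be counted without improving, and far fewer are. Responders under *or* with no fall in AHI are 0.1–1.8% of the TORS arm at 24.0, 0.02–0.9% at 16.4, and 0.3–2.1% of an arm with mean 34.0 and SD 10.0. At 2% of 25, that is half a patient. At TORS mean 24.0, 93–99% of the *and*/*or* gap is patients whose AHI fell but who met only one condition.

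**The case against.** The strongest reply is that the named criteria fix the connective, and that an article condenses a fuller protocol. But the article never states those criteria, and the words that stand beside the label are *and or*. If the criteria do settle it, the article's wording departs from them or blurs them; the line needs correcting either way. This is a stated definition that is ambiguous, not detail left to another document.

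A second reply is that this is a typographic slip. List numbers and citation numbers are visibly run together in the same sentence, and a slash may have been lost. Restoring it gives *and/or*, which is no clearer, or is the inclusive *or* that fits badly here.

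A third is that refusing to count 80 to 40 is a preference about what a response should be. That is fair. The argument from the entry limit is different: it follows from the trial's own numbers.

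The objections to size stand in full. A reader might infer that *or* would credit many patients who did not improve; the figures above put this at about 2% of an arm at most. A reader might call this the trial's headline success rate. The article does not: mean AHI is primary, this item is exploratory, and section 2.5 does not call it success. A reader might also quote an arm difference of 15–25 points under *and* against 38–41 under *or*. That comparison sets the control follow-up mean at 34.0, close to the assumed baseline, so that CPAP or MAD has no average effect. The Introduction says both reduce AHI, and 34.0 is a planning input, not a forecast.

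**Conclusion.** The point holds as an ambiguous outcome definition, one reading of which can be met at baseline by patients the trial admits. That part rests on the text and on logic alone.

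The size depends on a baseline distribution and a correlation that the article does not give. Over the ranges tried around a mean of 30 to 35, the choice of connective moves the TORS responder rate from roughly a fifth to nearly a half at the planning values, and from somewhat over a half to about three quarters at the centre's own values. I offer no figure for the difference between arms.

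The primary endpoint, sample size and power are unaffected. The correction is worth making because the definition is the yardstick for later reporting and costs almost nothing to settle.

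**What to change.** In section 2.5 replace *and or* with *and*: AHI at 6 months reduced by at least 50% from baseline and also below 20/h. Of the two readings, it is the only one that requires a fall in AHI from every patient admitted at 15 or above. Apply it identically in both arms and report each component separately beside it. Check the wording against the cited criteria and the full protocol so that all versions agree, and fix it before any between-arm comparison of 6-month polygraphy data.

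The cost is one word in the definition and no new data. The downside is a lower responder rate than under *or*; reporting the components keeps that visible.

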**Study objective:**

This study aims to evaluate whether base of the tongue (BOT) reduction using TORS is equal or superior to CPAP and MADs in improving quality of sleep and life in patients with moderate to severe OSA eligible for surgery.

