Other study parameters will be descriptive parameters such as age, gender, body mass index, history of smoking, reflux complaints, dentition, history of medication use including sleep medication, physical examination (Friedman score of the tongue tonsils and throat tonsils), measurements of DISE such as tongue base collapse classified by velum oropharynx tongue base epiglottis classification system (VOTE) [24]. Other PSG measurements are also included as study parameters such as ODI 4%, lowest desaturation (LSAT), desaturations below 90%, number of hypopneas, number of apneas and snoring time. For CPAP and MAD compliance will be assessed by pulmonologists and maxilla oral facial surgeons including follow up time, start date of treatment. Quality of life assessments and swallowing quality through MDADI [18] and SWAL-QoL [20] at baseline 3 months, 6 months and 12 months for the TORS group.

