After inclusion and randomization, group 1 will undergo TORS and will be hospitalized post-surgery, which is expected to be 3 days. Patient will be discharged home with pain medication and will visit the outpatient clinic after 6 weeks for evaluation of surgical wounds. Group 2 will be assessed by either a pulmonologist or a MFO surgeon. They will have an evaluation of treatment after 3 months. Time point 0 (T0) starts when patient undergoes surgery and the first day of usage of CPAP or MAD. The TORS group will complete questionnaires at 3, 6 and 12 months and will undergo PG at 6 and 12 months for evaluation of the treatment. Then, they will also have evaluation of swallowing quality of the speech language pathologist at baseline, 2 days after surgery (while hospitalized) and 6 weeks. The CPAP or MAD group will have outpatient follow-ups at the pulmonologist or MFO surgeon at the same time points. Then, they will also complete the questionnaires (3,6 and 12 months) and will undergo PG at 6 and 12 months. The CPAP will be read out at 3,6, and 12 months. For the TORS group, in addition to standards PG and quality of life questionnaires, pain scores using VAS will be recorded. The length of hospital stay will also be monitored.

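### No baseline EQ-5D-5L is stated for both arms, so, followed as written, the plan cannot report change in generic quality of life and loses precision

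*Protocol article*

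**What the plan says.** Section 2.5 (Study outcomes) lists as a secondary outcome "differences between scores of quality of life questionnaires EQ-5D-5L [19] at 3 months, 6 months and 12 months". Section 2.6 (Recruitment and screening) gives the same times for the questionnaires as a block. For surgery: "The TORS group will complete questionnaires at 3, 6 and 12 months and will undergo PG at 6 and 12 months". For the control arm: "they will also complete the questionnaires (3,6 and 12 months) and will undergo PG at 6 and 12 months". Section 2.10 (Statistical analysis) describes the baseline table as "Baseline characteristics, including age, gender, BMI, PG, ENT exam, DISE results, smoking, and reflux history"; no questionnaire score is named.

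The Abstract sets the objective as whether TORS is equal or superior in "improving quality of sleep and life in patients with moderate to severe OSA", and the Introduction says that health-related quality of life will be evaluated in both groups.

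One further sentence in 2.5 bears on the point: "Quality of life assessments and swallowing quality through MDADI [18] and SWAL-QoL [20] at baseline 3 months, 6 months and 12 months for the TORS". It names a baseline, but for two swallowing instruments and for the surgical arm.

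On analysis, 2.10 compares the arms at follow-up with unadjusted tests, foresees no adjustment for baseline differences, applies the same approach to secondary outcomes, and does not replace missing data.

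**The concern.** EQ-5D-5L is the only generic quality-of-life instrument assigned to both arms; MDADI and SWAL-QoL are for the TORS group. If it is collected only at the times stated, the trial can say which arm scores higher at 3, 6 or 12 months, but not whether patients in either arm got better or worse. With 25 per arm, a chance difference in starting quality of life could be neither seen nor adjusted for, and the precision that a baseline covariate would bring is lost. Sections 2.8 and 3 say that interpretation will rest on effect estimates and confidence intervals, so the width of those intervals matters. A score not taken before treatment cannot be recovered later.

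**Working it through.** **1. What the text states about baselines, measure by measure**

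| Measure | Follow-up times stated | Baseline stated or implied? |
|---|---|---|
| VAS snoring, tiredness, globus (2.5) | 3, 6, 12 months | Yes, all patients |
| FOSQ-35 (2.5) | 3, 6, 12 months | Implied: 10% increase is relative to baseline |
| ESS (2.5, 2.6) | 3, 6, 12 months | Implied: part of the diagnostic work-up |
| ODI 4% (2.5) | 6, 12 months | Implied: relevance is relative to baseline |
| Polygraphy | 6, 12 months (2.6) | Yes, in 2.5; omitted from the 2.6 schedule |
| MDADI, SWAL-QoL (2.5) | 3, 6, 12 months | Yes, TORS group |
| EQ-5D-5L (2.5, 2.6) | 3, 6, 12 months | Not stated or implied for both arms |

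Two things follow. EQ-5D-5L is the one questionnaire for which nothing in the text supplies a clear baseline. But the time lists are not complete collection schedules, because they omit the polygraphy and FOSQ-35 baselines too.

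**2. Check of the method on the plan's own figure**

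The document gives no precision or power figure for EQ-5D-5L. For the primary endpoint it gives 82% power with 21 per arm, difference 10.0, SDs 10.0 and 12.0, two-sided 5% (2.8). The standard error is sqrt((10² + 12²)/21) = sqrt(11.62) = 3.41, so the noncentrality is 10/3.41 = 2.93. The noncentral t distribution with 40 degrees of freedom gives 81.7%. The stated figure reproduces, and the same t-based method is used below.

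**3. Chance imbalance at baseline**

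In SD units, the SD of the between-arm baseline difference is sqrt(2/n). With n = 25 this is sqrt(2/25) = 0.283, so the 95% range is ±1.96 × 0.283 = ±0.55 SD. The difference exceeds 0.25 SD in about 38% of such trials and 0.5 SD in about 8%.

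Only a fraction r, the baseline-to-follow-up correlation, is expected to reach the follow-up difference. An imbalance of 0.55 SD becomes 0.3 × 0.55 = 0.17, 0.5 × 0.55 = 0.28 or 0.7 × 0.55 = 0.39 SD.

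**4. Precision with and without adjustment, 25 per arm**

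Adjusting for baseline multiplies the standard error by sqrt(1 − r²). The correlation is not in the document; 0.3 to 0.7 is assumed. The 95% half-width is t × sqrt(1 − r²) × 0.283, with 48 degrees of freedom unadjusted and 47 adjusted.

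| r | sqrt(1 − r²) | Cut in standard error | 95% CI half-width (SD) | Detectable at 80% power (SD) |
|---|---|---|---|---|
| unadjusted | 1.000 | – | 0.57 | 0.81 |
| 0.3 | 0.954 | 5% | 0.54 | 0.77 |
| 0.5 | 0.866 | 13% | 0.49 | 0.70 |
| 0.7 | 0.714 | 29% | 0.41 | 0.58 |

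With 20 per arm (25 × 0.8, if 20% are missing), the detectable difference goes from 0.91 SD unadjusted to 0.87, 0.79 and 0.65 SD.

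**The case against.** The strongest reply is that the baseline may well exist. The 2.6 schedule omits baseline polygraphy, which 2.5 explicitly includes, and its questionnaire block covers FOSQ-35, whose responder rule needs a baseline. The baseline list in 2.10 is introduced as non-exhaustive and omits every questionnaire, so its silence proves nothing about this one. The MDADI sentence opens with quality-of-life assessments in general and could be read as covering EQ-5D-5L, though its closing words point to the TORS group. The design figure and the full protocol are not shown. All of this stands. A reader might infer that EQ-5D-5L is definitely collected only after treatment; the documents do not support that, only that no baseline for both arms is stated.

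A reader might also infer that the quality-of-life comparison is biased, or that a chance imbalance passes whole into the later differences. Neither follows. Randomisation keeps the comparison at each visit valid, the outcome is defined as a difference between scores, only the correlated part of an imbalance persists, and the ordinary confidence interval already allows for it.

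Finally, the precision gain comes from the adjusted analysis, not from the form alone. Under 2.10 as it stands, a baseline score would not enter the test. That is correct, and it is why the remedy must change the analysis text as well as the schedule.

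What the reply does not remove is that, on each reading, the baseline is absent, unclear or stated for one arm, and the planned analysis would not use it.

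**Conclusion.** The point holds as a gap in what is stated, together with an avoidable loss of information if the text is followed as it stands. Change in generic quality of life could then not be reported in either arm. The between-arm comparison would be unbiased but less precise than it could be: a standard error about 5% to 29% larger than what adjustment would remove, expressed as a share of the unadjusted value, and a detectable difference of about 0.81 SD instead of 0.77 to 0.58 SD. These figures assume 25 evaluable patients per arm, equal SDs, roughly normal scores and a correlation of 0.3 to 0.7 that the document does not give; at 0.3 the gain is small. EQ-5D-5L is secondary and 2.8 treats secondary outcomes as exploratory, so the primary endpoint and the sample size are untouched. The change is worth making because it is cheap on either reading and a missed baseline cannot be collected afterwards.

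**What to change.** - **2.5 (item 6) and 2.6:** state EQ-5D-5L at baseline, 3, 6 and 12 months in both arms, with the baseline form completed after consent and before the envelope is opened. The order matters because the trial is unblinded and knowing the allocation could colour the answers.
- **2.10, baseline table:** add the EQ-5D-5L score.
- **2.10, analysis:** report the TORS minus non-surgical difference in EQ-5D-5L at each visit, adjusted for the baseline score, with its 95% confidence interval. Give change from baseline per arm as description only.
- **2.10, consistency:** amend the sentence that foresees no baseline adjustment so that it allows this one. Add an exception to the rule that missing data are not replaced: patients already enrolled without a baseline form stay in the analysis with the overall mean baseline score (both arms pooled) as their covariate value. Without these two edits the new analysis would contradict the section.

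The cost is one short form (five items and a 0–100 scale) and the wording changes; no extra patients are needed. Some patients already enrolled may lack a baseline score; they remain in the comparison but add nothing to the precision gain or to the description of change. If a baseline form is already in use in both arms, only the wording and the analysis change.

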## Introduction

1

In obstructive sleep apnea (OSA) syndrome, repetitive partial or complete collapse of the upper airway during sleep leads to nocturnal hypoxia and interruption leading to daytime sleepiness [1]. OSA is associated with an increased risk of comorbidities such as hypertension, type 2 diabetes mellitus, and cardiovascular disease [2,3]. The gold standard treatment for OSA is continuous positive airway pressure (CPAP). CPAP effectively reduces apnea hypopnea index (AHI), improves sleep quality and decreases cardiovascular co-morbidities [4,5]. Regardless of the benefits, 30% of patients refuse treatment with CPAP due to several reasons including pressure effect of the mask [4] [[5], [6], [7]]. Another challenge of CPAP is treatment adherence, which requires a minimum usage of 4 h per night on at least 70% of nights. A study by Koehler et al. has shown that after 3 months adherence rates were 54% [8]. Mandibular advancement devices (MADs) are another non-surgical treatment modality that effectively reduce AHI [9], though they are less effective than CPAP. However, MADs demonstrate higher treatment adherence compared to CPAP [10].

For OSA patients who are unable to tolerate CPAP or MADs and are eligible for surgery, transoral robotic surgery (TORS) has emerged as an effective treatment option. TORS focuses on the obstruction at BOT, permanently enlarging the upper airway by removing lingual tonsil tissue. However, like all surgeries, TORS carries inherent risks such as postoperative bleeding, stenosis, infection and dysphagia, all risks that non-surgical therapies do not present. While studies have shown that TORS effectively reduces AHI [11,12], randomized trials comparing its efficacy to standard non-surgical therapies are lacking.

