In this proposed study, a trial designed to address a clinically pragmatic question: whether TORS, an accepted surgical treatment for selected patients but typically positioned after non-surgical therapies in the routine care pathway, provides outcomes that are equal or superior to standard non-surgical management. In this parallel-group, randomized controlled trial with a 1:1 allocation ratio, we will compare TORS to non-surgical therapy (CPAP or MADs). Following a superiority framework, it aims to determine whether TORS provides better sleep outcomes, long-term efficacy, and quality of life while assessing complications, compliance, and functional outcomes. These comparators were chosen because CPAP and MADs are well-established, non-invasive treatments recommended in clinical guidelines and are typically chosen as first options in routine care. Historically, surgery has been considered a last resort in the management of OSA. Therefore, CPAP and MAD are pooled as non-surgical therapy in this trial to reflect real-world conventional management rather than to compare TORS against a single treatment modality. The primary objective of this study is to quantify the effectiveness of TORS relative to CPAP or MADs in treating OSA. Additionally, this study aims to determine the long-term outcomes of TORS compared to conventional therapy, assess functional sleep outcomes in patients undergoing TORS. Furthermore, it will evaluate health-related quality of life in both treatment groups and examine patient compliance with non-surgical therapy. By addressing these objectives, this study aims to provide comprehensive insight into the role of TORS as a treatment modality for OSA, helping to inform clinical decision-making and improve patient outcomes.

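### Swallowing and taste are scored only in the TORS arm, so the trial yields an uncontrolled before-after change for them and no between-arm estimate

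*Protocol article*

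**What the plan says.** In the protocol article, section 2.5 (Study outcomes), the last secondary outcome is "VAS scores swallowing and taste for patients in the TORS group at baseline compared to 3 months, 6 months and 12 months". The outcome just before it is "differences in scores on the visual analogue scales (VAS) for snoring, tiredness and globus in all patients between baseline, 3, 6 and 12 months". The two items share the same type of scale and the same visits, but only the earlier one covers both arms.

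Later in section 2.5, MDADI and SWAL-QoL are scheduled "at baseline 3 months, 6 months and 12 months for the TORS group". Section 2.6 (Recruitment and screening) adds, for TORS patients, an "evaluation of swallowing quality of the speech language pathologist at baseline, 2 days after surgery (while hospitalized) and 6 weeks". For the CPAP or MAD group the same section says "Then, they will also complete the questionnaires (3,6 and 12 months) and will undergo PG at 6 and 12 months", without listing which questionnaires are meant.

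The Introduction states that "TORS carries inherent risks such as postoperative bleeding, stenosis, infection and dysphagia, all risks that non-surgical therapies do not present", and that the trial will compare outcomes "while assessing complications, compliance, and functional outcomes".

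**The concern.** The protocol itself names dysphagia as a hazard of the surgical arm, yet every swallowing or taste measure that it assigns to an arm goes to TORS. A change from baseline in one arm is not a randomised comparison. It combines what surgery did with whatever would have happened anyway over 12 months of repeated scoring.

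The Discussion says the results should help decide whether surgery belongs earlier in the treatment pathway, and the participants have not been treated with CPAP or MAD before. That decision weighs benefit against harm. AHI, ODI, ESS, FOSQ-35 and EQ-5D-5L will each have a between-arm comparison, but measured swallowing and taste will not.

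**Working it through.** **The plan's own figures.** The protocol gives no effect size, SD or precision for any swallowing or taste measure, so there is no figure on this point to reproduce. Its one power statement (section 2.8) concerns AHI: 21 per arm, difference 10.0, SDs 10.0 and 12.0, two-sided alpha 0.05. With SE = sqrt(100/21 + 144/21) = 3.41, the noncentral t gives 81.7%, which agrees with the stated 82%. That does not bear on this point, but the sizes of 21 and 25 per arm are used below.

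**Which arm gets which measure**

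| Measure | Arm as written | Section |
|---|---|---|
| VAS swallowing | TORS only | 2.5 |
| VAS taste | TORS only | 2.5 |
| MDADI, SWAL-QoL | TORS only | 2.5 |
| Speech-language pathologist evaluation | described for TORS only | 2.6 |
| VAS snoring, tiredness, globus | all patients | 2.5 |
| EQ-5D-5L | no restriction by arm | 2.5 |
| Adverse events, if reported or observed | no restriction by arm | 2.11 |

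No swallowing or taste measure is explicitly assigned to the control arm. Five are assigned to TORS: two VAS items, two questionnaires and the pathologist's evaluation.

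**What a one-arm change estimates.** Let S be the effect of TORS on the score, C any effect of CPAP or MAD, and B the change that would occur anyway through time and repeat testing.

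- TORS arm, change from baseline: S + B
- Control arm, change from baseline, if collected: C + B
- Difference between arms: (S + B) − (C + B) = S − C

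The plan observes only S + B, so S can be read off only by assuming that B is zero. With controls, B cancels by randomisation.

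**Precision if both arms were scored.** The results are in SD units because no SD is given. An equal SD in both arms is assumed. The half-width of the 95% interval for a difference in means is t(2n − 2; 0.975) × sqrt(2/n).

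- n = 25 per arm: 2.011 × sqrt(2/25) = 2.011 × 0.283 = 0.57 SD
- n = 21 per arm: 2.021 × sqrt(2/21) = 2.021 × 0.309 = 0.62 SD

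The second case matters because section 2.8 allows for missing data down to 21 per arm. The difference detectable with 80% power (noncentral t, two-sided 0.05) is 0.81 SD with 25 per arm and 0.89 SD with 21. Power for a difference of 0.5 SD is about 41% and 35%. Adjusting for the baseline score would narrow the intervals by an amount that depends on the correlation between baseline and follow-up, which the protocol does not give.

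**The case against.** The strongest reply is that this is a deliberate choice. If non-surgical therapy carries no dysphagia risk, as the Introduction says, the control change should be near zero, and following patients from a prospective baseline is a common way to watch for a procedure-specific harm. Sections 2.5 and 2.6 are largely consistent in doing so, and nothing in the protocol promises a randomised comparison of swallowing or taste. This stands to the extent that the plan is not contradicting itself. But a treatment with no dysphagia risk fixes only C at zero. It says nothing about B, or about how common swallowing complaints already are in these patients.

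Several stronger readings are tempting, and the protocol does not support them:

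- *Harm is not compared between arms, so benefit and harm cannot be weighed.* Adverse events, globus VAS and EQ-5D-5L cover both arms. The gap is confined to measured swallowing and taste.
- *Regression to the mean distorts the before-after change.* Section 2.2 selects on AHI, Friedman grade and DISE findings, not on swallowing or taste scores, so there is no stated reason to expect it.
- *Swallowing and taste are the main functional harm.* The Introduction lists dysphagia beside bleeding, stenosis and infection without ranking them, and does not name taste.
- *A promised comparison of functional outcomes is broken.* The Introduction later speaks of functional sleep outcomes, which fits the FOSQ-35. The firmer basis is the statement that complications will be assessed.

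It is also fair to say that the stakes are limited. Secondary outcomes are exploratory (section 2.8), MDADI and SWAL-QoL are descriptive parameters, and the AHI result is untouched. The trial is unblinded, so a self-rated comparison could carry expectation effects. Finally, the questionnaires that controls complete are not itemised in section 2.6, and section 2.4 describes MDADI and SWAL-QoL without naming an arm. The full protocol might say more, but section 2.5 is explicit.

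**Conclusion.** The concern holds in a limited form. As written, the trial can give only an uncontrolled before-after change for swallowing and taste, although it names dysphagia as a TORS risk and says it will assess complications. The measures that do cover both arms do not fill the gap: globus is a different symptom, the EQ-5D-5L domains include neither swallowing nor taste, and adverse events depend on being reported or noticed in an open trial.

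Scoring both arms would replace no between-arm estimate with one whose unadjusted 95% half-width is about 0.57 SD (25 per arm) to 0.62 SD (21 per arm), assuming equal SDs. That is enough to show or exclude large differences, not moderate ones. A very large harm would probably be visible without controls. A moderate change could not be attributed securely to surgery under the present plan. This is a worthwhile, inexpensive improvement and does not threaten the primary conclusion.

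**What to change.** In section 2.5, move the swallowing and taste VAS into the item that already covers all patients, so that both arms are scored at baseline, 3, 6 and 12 months together with snoring, tiredness and globus. Report the between-arm difference at each follow-up with a 95% confidence interval, adjusted for the baseline score, and label it exploratory. Section 2.10 says that adjustment for baseline differences is not foreseen, so it needs a line allowing it for these two outcomes. State that the ratings are unblinded.

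In section 2.6, list the questionnaires that control patients complete so that it agrees with section 2.5. MDADI in controls could be added if burden allows, but the fix does not need it.

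The cost is two extra VAS lines for control patients at time points when they already complete three, with no additional patients or visits.
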